## Methods/Design

### Design, ethics approval and registration

This pilot trial is an explorative mixed-methods intervention study with pre-test and post-test. The ethical review board of the cantons Basel Stadt and Basel Land (Switzerland) approved the proposal on the September 16th, 2010 (reference no. 224/10). The trial has been registered at Current Controlled Trials as ISRCTN24344776.

### Setting and Sample

Reasoning on sample and sample size for this pilot, we followed Thabane et al. [18], who recommend orientation at the feasibility criteria (see below). From this point of view, the present study does not allow sample size calculation. Consequently, inference statistics is not intended.

In order to avoid side effects, all eligible residents and all nurses in charge of them should be asked for participation in the study and offered Kinaesthetics training, respectively. On one hand, we considered a nursing home of typical size to yield a sufficient number of participants on the resident as well as the staff level. On the other hand, conducting the trial with two or more centres could be a waste of resources in case of feasibility problems.

The trial is conducted in a nursing home of the canton Basel, Switzerland, with 76 residents and 60 nursing staff. All seniors, who fulfil the inclusion criteria, will be asked to participate. According to the head nurse, 22 residents are eligible at the moment. For this feasibility study, 36 nurses who are regularly in charge are included. Based on the fact that usually about 5% of the persons asked do not wish to participate and 10% will drop out, the final sample size is estimated 19 residents.

Concerning the sample size of the nurses, it is assumed that about 5% of the persons asked that had the Kinaesthetics training would not like to participate and 10% will drop out. Consequently, the final sample size of the nurses is estimated about 31.

On the staff level, inclusion criteria are:

• participation in the Kinaesthetics training course during trial

• no Kinaesthetics training before

• informed consent

On the resident level, inclusion criteria are:

• needs assistance in mobility

• physical condition allows for participation

• can read and speak German

• is able to understand the study information

• informed consent

### Intervention and measurement points

The duration of the study will take 30 months from September 2010 to December 2012, the intervention will start in October 2010. The process and time schedule is shown in Figure 2. Measurements will be taken on the staff level and on the resident level as well. The whole training course and practice counselling will be carried out by an external licensed Kinaesthetics trainer who is not involved in this study.

**Figure 2 F2:**
[figure not shown]
**Flowchart of the study**.

After the T0 measurement point (pre-test) all nurses will be trained in a basic course in Kinaesthetics for 4 days and have practice counselling of 1 day within 4 months. 36 nurses will be trained in two groups, each of 18 nurses. After this, first post-test (T1) will take place. An advanced course in Kinaesthetics will be held 10 months after the basic course for 4 days within 4 months, before T2. At T0, T1 and T2, mobilisation of patients will be recorded on video, e.g. mobilisation out of bed and from bed to chair and backwards, walking with aid and positioning in bed. At T1 and T3, nurses will be invited to focus group discussions.

### Primary outcome measures

The outcome measures refer to the feasibility criteria described in chapter "Reasons and objectives of the pilot trial and criteria of feasibility". There are measurements on the staff level and on the resident level.

#### Resource-oriented feasibility

At T2, residents as well as staff will be asked if they once more would take part in the study. Using the percentage of negative replies and the drop-out rate, feasibility criteria RES_1 and RES_2 can be calculated. RES_3 (missing values) will be calculated after data processing.

#### Science-oriented feasibility

Immediately after each transfer recorded at T0, T1 and T2, the residents will be asked about the safety, comfort, pain and one's own participation during the transfer with a questionnaire. The scale ranges for pain from 0 = no pain to 5 = unbearable pain; for safety from 0 = very unsafe to 5 = very safe; for comfort from 0 = very uncomfortable to 5 = very comfortable and for participation from 1 = very low participation to 5 = very high participation. The feasibility criteria SCI_1 and SCI_2 will be calculated after data processing.

Immediately after every transfer recorded at T0, T1 and T2 the nurses will be asked about the subjectively perceived physical strain during patient transfer. The data will be collected with the Borg CR10 scale of perceived strain, with a scale from 0 = no strain at all to 10 = extreme strain after every patient transfer (SCI_4) [21].

The movement competence of the nurses will be measured with the SOPMAS Instrument (Structure of the Observed Patient Movement Assistance Skill) (SCI_5). It observes each nurse's individual performance and learning in patient transfer tasks and patient participation in locomotion activities with 4 items: interaction, patient's movement, the nurse's posture and movement, environment and auxiliary devices. The scale ranges from 1 = no skills to 5 = very good skills. All scale levels were given specific definitions, suited for patient transfer situations. The instrument was tested and compared with the Swedish DINO instrument [22] of which validity and reliability have been tested. The correlation was tested by the Pearson test and was good (r = 0.72), though there was a level difference. The highest level of the SOPMAS was missing in the DINO [12]. Video recordings of two transfers of each nurse, e.g. bed-wheelchair/chair-bed, transfer in bed (positioning) will be recorded at the measurement points at the baseline before training (T0), within one month after the basic course (T1) and within one month after the advanced course (T2). The feasibility criteria SCI_3 of the residents for the Item patient's movement and the score over all items SCI_5 for the nurses will be calculated after data processing.

#### Process-oriented feasibility

The reasons of residents and staff leaving the programme will be discriminated. Adverse events (AE) are considered in the process-oriented feasibility. Therefore, the whole number of drop-outs will be diminished by the drop-outs due to AE. Leaving the programme on one's own decision should be 50% or less for the residents (PRO_1), and 30% or less for the nurses (PRO_2).

### Secondary outcome measures

Further outcomes should yield additional information, especially for improvements of the intervention and the research design, and for obtaining information of possible effects. In order to reach this goal, there are quantitative and qualitative measurements on the staff level and on the resident level.

#### Nursing staff level

##### Socio-demographic data

Age, sex, education, profession and musculoskeletal disorders will be recorded with a questionnaire at T0.

##### Knowledge, skills, application, motivation and benefits of Kinaesthetics

A structured questionnaire about knowledge and skills (7 Items, with scaling from totally agree to totally disagree), application (9 items, with scaling from totally agree to totally disagree), motivation (11 items, with scaling from totally agree to totally disagree) and benefits (7 items, with scaling from no benefit to very great benefit) was developed by the primary investigator ([name]), Kinaesthetics trainers and peer tutors from Germany, Finland and Switzerland. The content validity of the German version was tested by two Kinaesthetics trainers and seven nurses who were in training as peer tutors. The measurement points are within one month after the basic course (T1) and within one month after advanced course (T2).

##### Learning and transfer of Kinaesthetics in the daily working routine

There will be 2 focus group interviews for the nurses participating in this study with questions about the importance of movement in nursing care, experience with the learning process and the transfer of Kinaesthetics in clinical practice. The measurement point will be after the basic course (T1) and within six months after the advanced course (T3).

#### Resident level

##### Socio-demographic data

Age, sex, movement problems, need for movement assistance, pain medication, participation in the in-house movement group will be recorded with a questionnaire at T0.

##### Functional mobility

The MOTPA instrument (mobility test for residents in acute care) [23,24] observes the amount of assistance needed in 11 functional tasks, which includes

- Lying in the bed: moving to the top, moving sideways, transfer from supine to lateral position, transfer from lateral lying position to sitting on the edge of the bed

- Sitting on the edge of the bed: moving forward, keeping a sitting position, standing up

- Standing position: turning 180°, going backwards 3 steps, short walk (6 meters), walk (30 meters), sitting down.

The mobility profile will be assessed from the same video recordings mentioned above. Measurement points are within one month after basic course (T1) and within one month after advanced course (T2).

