**Methods/Design:**

Standard basic and advanced Kinaesthetics courses (each comprising four subsequent days and an additional counselling day during the following four months) are offered to n = 36 out of 60 nurses in a residential geriatric care home, who are in charge of 76 residents. N = 22 residents needing movement support are participating to this study.

On the staff level, measurements include focus group discussions, questionnaires, physical strain self-assessment (Borg scale), video recordings and external observation of patient assistance skills using a specialised instrument (SOPMAS). Questionnaires used on the resident level include safety, comfort, pain, and level of own participation during mobilisation. A functional mobility profile is assessed using a specialised test procedure (MOTPA).

Measurements will take place at baseline (T0), after basic training (T1), and after the advanced course (T2). Follow-up focus groups will be offered at T1 and 10 months later (T3).

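### Residents' functional mobility (MOTPA) is scheduled at T1 and T2 only, although the videos it is rated from are also made at T0, so the plan yields no pre-post change in mobility

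*Protocol article*

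**What the plan says.** **MOTPA schedule.** Under Secondary outcome measures, Resident level, Functional mobility: "Measurement points are within one month after basic course (T1) and within one month after advanced course (T2"). T0 is not listed and no reason is given.

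**Source of the ratings.** Same section: "The mobility profile will be assessed from the same video recordings mentioned above".

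**When those videos are made.** Under Intervention and measurement points: "At T0, T1 and T2, mobilisation of patients will be recorded on video". Under Science-oriented feasibility, two transfers per nurse "will be recorded at the measurement points at the baseline before training (T0), within one month after the basic course (T1") and again after the advanced course. The first of these sections calls T0 the pre-test.

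**Design and purpose.** Under Design, ethics approval and registration: "This pilot trial is an explorative mixed-methods intervention study with pre-test and post-test". The abstract wants effect estimates to help decide on and prepare a controlled trial. The introduction to the secondary outcomes gives information on possible effects as one of their purposes.

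**Tasks and missing data.** MOTPA "observes the amount of assistance needed in 11 functional tasks", followed by a list in three groups. In Table 2, RES_3 requires fewer than 50% missing values for MOTPA.

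**The concern.** With no control group, a resident's own value before staff training is the only reference for an effect. The logic model expects trained nurses to bring about higher movement competence in residents, and MOTPA is the one instrument the article lists for functional mobility. If it is first rated after the basic course, any gain from that course is already in the first value and cannot be seen.

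The plan describes a two-stage training. Of the changes that would inform a later trial (first stage, second stage, whole programme), only the second-stage change remains for mobility. The material for the other two is being recorded anyway.

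The schedule also reaches a primary feasibility criterion, because the number of planned MOTPA values is the denominator of its part of RES_3. The disagreement between stated and listed tasks affects the same denominator.

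**Working it through.** **1. Number of residents.** Setting and Sample gives 22 eligible, 5% refusing, 10% dropping out and a final sample of 19.

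- 22 × 0.95 × 0.90 = 18.81, which rounds to 19. The stated figure reproduces.
- Adding the two losses instead: 22 × 0.85 = 18.70, also 19.

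**2. Time points, side by side.**

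| Item | T0 | T1 | T2 |
|---|---|---|---|
| Video recordings | yes | yes | yes |
| SOPMAS (from the videos) | yes | yes | yes |
| Resident ratings after each recorded transfer | yes | yes | yes |
| MOTPA (from the same videos) | not listed | yes | yes |

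**3. Profiles and paired changes.**

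- As written: 2 × 19 = 38 profiles (2 × 22 = 44 if every eligible resident joins and stays). None precedes training, so 0 of 19 residents have a T0-T1 or T0-T2 change.
- With T0 rated: 3 × 19 = 57 profiles (3 × 22 = 66), and up to 19 (22) residents have a change from T0.
- Difference: 57 − 38 = 19, or 66 − 44 = 22 additional profiles.

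**4. What the remaining contrast measures.** Let *a* be the mean change from T0 to T1 and *b* the mean change from T1 to T2. The whole-programme change is *a* + *b*. The written schedule gives *b* alone. If mobility improves after the basic course and then holds, *b* is about zero while *a* + *b* is positive. If it improves early and then declines, *b* is negative. Nothing collected on MOTPA could distinguish either case from a training without effect.

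**5. Task count.** The list has 4 tasks lying, 3 sitting and 5 standing: 4 + 3 + 5 = 12, against the stated 11. If RES_3 is counted per task, the planned number of values for 19 residents is:

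| | 11 tasks | 12 tasks |
|---|---|---|
| Two time points | 19 × 2 × 11 = 418 | 19 × 2 × 12 = 456 |
| Three time points | 19 × 3 × 11 = 627 | 19 × 3 × 12 = 684 |

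If it is counted per profile, the task count does not matter and only the number of time points does.

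**The case against.** **It may be a drafting slip.** The MOTPA timing sentence closely matches the one for the nurses' questionnaire on knowledge, skills and application, which is also T1 and T2 only. The time schedule is in Figure 2, which is not shown here, so it cannot be checked. This stands as a reason not to call the omission deliberate. It does not remove the need to correct it. The questionnaire asks about Kinaesthetics, in which included nurses have had no earlier training, so a missing baseline makes sense there. Residents' mobility exists before training.

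**The abstract.** A reader might infer a direct contradiction from "Measurements will take place at baseline (T0), after basic training (T1), and after the advanced course (T2"), which follows soon after MOTPA is named. The documents do not support that much. The sentence is general, does not name MOTPA, and is not true of every instrument, as the nurses' questionnaire shows.

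**RES_3.** A reader might infer that one third of MOTPA values are missing from the start. That holds only if T0 counts as planned and is left unrated. The limit would then be 1/3 + (2/3)*m* < 0.50, so *m* < 0.25 at T1 and T2. On the schedule as written, T0 values are not planned and so not missing. Even at one third, the 50% limit is not breached.

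**Other resident data at T0.** The SOPMAS item on patient's movement (SCI_3) and residents' rated participation (part of SCI_1) are collected at all three points. It would therefore be wrong to say that the resident level has no pre-post data. Neither is a functional mobility profile, however, and the T0 questionnaire on movement problems and need for assistance is not scheduled again.

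**Coverage of the videos.** The recordings are two transfers per nurse, with examples such as bed to chair and positioning. Nothing shows that every MOTPA task, such as the 30-metre walk, is filmed for every resident. The 50% allowance, against 20% for SOPMAS, is consistent with incomplete coverage. This applies equally to T1 and T2, so it does not explain leaving out T0, but a full T0 profile cannot be promised.

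**Task count.** A reader might infer that the MOTPA score range is wrong. No score range is given, and whether the two walks form one item depends on sources not at hand. Only the mismatch of 11 stated and 12 listed can be asserted.

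**Conclusion.** The point holds in a limited form. The plan fixes MOTPA at T1 and T2 and so gives up the pre-training value of its only functional mobility instrument, while filming at T0 the material from which that value could be rated. As written, 0 of the expected 19 residents contribute a T0-T1 or T0-T2 change, and only a T1-T2 contrast remains.

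This rests on the MOTPA section being the operative schedule and on the T0 videos being comparable with those at T1 and T2, as the article describes them. The baseline is recoverable for as long as the T0 recordings are kept.

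Severity is moderate. MOTPA is secondary, no inferential statistics are intended, none of SCI_1 to SCI_5 uses it, and it enters the feasibility decision only through missingness in RES_3. What is lost is one descriptive effect estimate of the kind the study says it wants. The mismatch in the task count is a separate, minor inconsistency.

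**What to change.** 1. In Functional mobility, state that MOTPA is rated from the T0, T1 and T2 recordings, as far as the recorded tasks allow, and check that Figure 2 agrees.
2. Report each resident's change from T0 to T1 and from T0 to T2 descriptively, beside the T1-T2 change, with the number of residents and tasks that contribute.
3. Compute the MOTPA part of RES_3 over these three time points, and say whether a missing value is a task or a whole profile.
4. Reconcile the 11 stated tasks with the 12 listed, and use the settled number in RES_3.

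The cost is rating time for 19 more profiles (57 instead of 38), or 22 if all eligible residents take part and stay (66 instead of 44). No new recordings or visits are needed. If T0 is left out on purpose, the section should give the reason and say that MOTPA describes only the course from T1 to T2.

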## Discussion

This project focuses on the effects of Kinaesthetics training for nurses and residents in nursing homes for elderly people. As part of their training, nurses learn new content working on their own or through group and pair work. The focus of this work centres on nurses own movement competences -- working on the assumption that as practical-based learning is the best way to learn.

Nurses learn as a process, which is characterised by a relatively stable change in their behaviour, thought or sensation based on experiences or newly acquired knowledge [25]. This begs the question whether the requisite learning process is actually taking place and being successfully transferred into practice.

The difficulty of being able to prove the benefits of Kinaesthetics is that the cause interdependencies of this intervention are not linear, but multi-dimensional. On the one hand, the effectiveness of such complex interventions (interventions that have multiple interacting components) cannot be viewed from the sum of its individual parts, thereby making it difficult to evaluate by examining individual factors [26]. On the other hand, there is also the difficulty of transferring the information acquired during training into the next step. Implementing Kinaesthetics in practice requires carers to incorporate both the knowledge they have acquired from their training, as well as any new associated knowledge, into individual care scenarios and their daily work at nursing care [27]. The learning and development process is what is important here, not just learning a care technique. This brings about a change in carers' behaviour in their everyday work. The change in behaviour is a laborious process, which often fails due to a lack of time or the initial amount of extra work required.
